**Methods:**

This study is a nonrandomized, open-label, parallel-setting, prospective, monocentric clinical trial. The main aim of this study was to refine the diagnosis in patients with GBM with REP and to optimize subsequent radiotherapy planning.

Glioblastoma patients who develop REP within approximately 6 weeks after surgery will undergo ^11^C-methionine positron emission tomography (PET/CT) examinations. Target volumes for radiotherapy are defined using both standard planning T1-weighted contrast-enhanced MRI and PET/CT. The primary outcome is progression-free survival defined using RANO criteria and compared to a historical cohort with REP treated without PET/CT optimization of radiotherapy.

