The current standard of care for GBM is based on a multimodal approach combining the maximum possible and safe surgery, postoperative radiotherapy (RT), and chemotherapy (CHT) with alkylating cytostatic temozolomide (TMZ). Adjuvant therapy is usually started within 4 to 6 weeks after surgery, during which the patient recovers from surgery, and all necessary procedures (multidisciplinary indication committee, preparation of radiation plan, etc.) take place before further oncological treatment. The standard postoperative management of newly diagnosed patients with GBM has remained unchanged since the published results of the EORTC 26981–22981/NCIC CE3 trial (Stupp regimen), which completed patient recruitment as early as 2002 and published the findings in 2005. In this protocol, TMZ (75 mg/m^2^) is administered on days 1 to 42 concurrently with RT (60 Gy), followed by TMZ alone (150 to 200 mg/m^2^) on days 1–5 in six consecutive 4-week cycles. Coadministration of RT and TMZ improved survival from 12.1 months (with RT alone) to 14.6 months (with the addition of TMZ) (3). Due to a certain stagnation in the treatment of GBM in recent years, intensive research at all levels is necessary to improve patients' perspectives on this unfavourable diagnosis.

The Perry accelerated regimen [8] is a treatment option for patients aged ≥ 65 years and those for whom long conventional RT (60 Gy in six weeks) combined with chemotherapy is considered unsuitable by their treating physicians. The total RT dose for this accelerated regimen is 40.05 Gy, administered in 15-day fractions over three weeks.

Concomitant TMZ is administered here at a dose of 75 mg/m^2^ per day for 21 consecutive days from the start of RT until its termination. As with Stupp's regimen, adjuvant TMZ alone follows at 150 to 200 mg/m^2^ daily for five consecutive days of a 28-day cycle, up to 12 cycles or until disease progression. For patients who are not candidates for concomitant chemoradiotherapy (regardless of age), individual adjuvant treatment is indicated as standard, usually accelerated RT alone (total dose 30–50 Gy in a 10–20-day dose, for example, fractionation regimens of 10 × 3.0 Gy, 10 × 3.4 Gy, 15 × 2.67 Gy, 20 × 2.5 Gy and others), followed in some patients by TMZ palliative chemotherapy based on the actual overall condition of the patient.

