#### Glioblastoma as a progressive disease

In connection with the greater availability of magnetic resonance (MR), it is possible to optimize the planning of radiotherapy according to the findings of the so-called planning MR for an increasing number of patients. It is an MR study performed immediately (approximately a few days) before the start of radiotherapy. Following the performance of this MR study (typically approx. 4–5 weeks after surgery), a new phenomenon called very rapid progression (REP, rapid early progression) is described. The REP diagnosis is based on comparing early postoperative MR findings (usually within 48–72 h after surgery) and planning MR before radiotherapy (preRT).

Retrospectively comparing early postoperative MR with preRT MR performed approximately 30 days later, Farace et al. described 30% of preRT MR with signs strongly suggestive of tumour progression during this period [9]. An even more significant proportion of patients with documented REP was described by Palmer et al., where up to 52% progressed before starting adjuvant therapy without any effect of waiting time to start RT (median time from resection to RT was 32.5 vs. 33 days in patients with REP vs. without REP (*p* = 0.337) [10]. These results are consistent with our retrospective analysis of 90 patients with GBM treated between 2014 and 2017, where 51% of patients had suspected REP at planning preRT MR [11]. These patients represent a subset with particularly aggressive GBM requiring further intensive research and possibly treatment modification.

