### Eligibility criteria {10}

A patient may be included in the clinical trial if they meet all of the following criteria:The participant is a person with a histologically proven diagnosis of glioblastoma (GBM) according to WHO 2016.The participants are male or female and aged 18 years or older.Performance status (PS) according to ECOG (Eastern Cooperative Oncology Group) 0–2.Healed operation wound.Postoperative MR up to 72 h.Indication for adjuvant chemoradiotherapy.The participants must express his/her informed consent and sign the form before the screening period.Rapid early progression was detected.The participants must achieve the following values of laboratory parameters in the peripheral blood during the screening period:neutrophils (total count) ≥ 1500/mm.3platelets (total count) ≥ 100,000/mm.3hemoglobin ≥ 9.0 g/dLserum creatinine ≤ 1.5 × of upper limit of normal (ULN)total bilirubin ≤ 1.5 × ULN, unless documented Gilbert's syndrome, for which bilirubin ≤ 3 × ULN is permitted AST/ALT ≤ 3 × ULN

The exclusion criteria were as follows:Prior brain surgery.Prior brain radiotherapy.The history of active/currently treated cancer (solid tumor) was as follows: nonmelanoma skin cancer, in situ bladder carcinoma, in situ gastric cancer, in situ colorectal carcinoma, in situ cervical carcinoma, and in situ breast cancer.Any systemic disease or health condition that might pose a risk for anticancer therapy and imaging techniques (MRI, MET PET).Patients must not have substance abuse disorders that would interfere with cooperation with the requirements of the trial.Patients must not have any evidence of ongoing (active) infection (HIV, hepatitis A, B, C).Pregnant and/or breastfeeding women.Patients who disagreed and refused to sign an informed consent form.

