### Outcomes {12}

Primary Outcome Measures of the clinical trial are to demonstrate the progression-free survival (PFS) in the 11C-methionine PET/CT arm as Experimental arm vs. PFS in the historical patient cohort as an arm Ahist. PFS was defined as the time from the start of radiotherapy to the progression of disease or death [Time Frame: 44 months].

The secondary outcomes are the following:

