Rapid-Early-Progression incidence [Time Frame: 38 months]Prospective evaluation of the incidence of Rapid-Early-Progression (REP) on planning MR in patients with GBM indicated for adjuvant chemoradiotherapy.Overall survival (OS) in the Experimental Arm vs. Arm Ahist [Time Frame: 44 months]OS in the Experimental Arm compared to the historical retrospective group (arm Ahist). OS = time from surgery to death related to glioblastoma multiforme.Biomarkers I [Time Frame: 38 months].Immunohistochemical analysis of GFAP, Ki-67, IDH1, ATRX, and PDL1. GFAP: positive/negative/focal positive Ki-67, IDH1: positive/negative, ATRX loss of expression: positive/negative, PDL1 protein expression: positive/negative.Biomarker II [Time Frame: 38 months]Mutational status of TERT and IDH2: mutated/wild-type.Biomarkers III [Time Frame: 38 months]Sanger sequencing of IDH1 in IDH1 IHC-positive patients: mutated/wild-type.Biomarkers IV [Time Frame: 38 months]MGMT promoter methylation status: ≥ 25% = methylated/ < 25% = unmethylated.Biomarkers V [Time Frame: 38 months]1 p/19 q codeletion: positive/negativePattern-of-failure analysis [Time Frame: 44 months]Evaluation of spatial patterns of failure (PoF; central (V95% ≥ 95%)/in-field (80% ≤ V95%)/marginal (20% ≤ V95% < 80%)/distant (V95% < 20%)) in patients with REP (the Experimental Arm) compared to the historical retrospective group (Arm Ahist). In the case of multifocal progression, each PD is evaluated independently, i.e., the patient could have one central and one distal PD. In subsequent statistical analysis, each PD was evaluated independently. PoF could be performed even in deceased subjects if MR describing the progression is available.Quality of Life assessment using the standardized European Organization for Research and Treatment of Cancer (EORTC) questionnaire QLQ-C30 [Time Frame: 44 months]Quality of life will be assessed using a standardized questionnaire: the European Organization for Research and Treatment of Cancer Quality of Life Questionnaire C30 v.3.0 during the screening period, visits 2, 4, 6, 8, 10, and 12 (End-Of-Treatment) and during the follow-up period every 3 months (± 1 week) up to progression of the disease.Quality of Life assessment using the standardized European Organization for Research and Treatment of Cancer (EORTC) Quality of Life questionnaire-BN20 [Time Frame: 44 months]Quality of life will be assessed using a standardized questionnaire: additional module Brain Cancer European Organization for Research and Treatment of Cancer Quality of Life questionnaire BN20 during the screening period, visits 2, 4, 6, 8, 10, and 12 (End-Of-Treatment) and during the follow-up period every 3 months (+/- 1 week) up to the disease.

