
### Participant timeline {13}

The schedule of enrolment, intervention and visits is summarized in Tables 1 and 2. The duration of the study participation is 44 months (recruitment 38 months + 6 months follow-up).

**Table 1 Tab1:** Participant timeline for the regimen according to Stupp

4.3.1.Stupp regimen	Screening	CHEMO RADIO THERAPY	Visit 1	Visit 2	Visit 3	Visit 4	Visit 5	Visit 6	Visit 7	Visit 8	Visit 9	Visit 10	Visit 11	Visit 12 (EoT)	Follow-up until PD	EoS Visit
Days / Months	**max. 14 D**	**D1-D42** **(M 1–2)**	**D42 + 1 M** (± 1 tweek)	** + 1 M**	** + 1 M**	** + 1 M**	** + 1 M**	** + 1 M**	** + 1 M**	** + 1 M**	** + 1 M**	** + 1 M**	** + 1 M**	** + 1 M**	**Every 3 M** (± 1 tweek)	**PD**
Inclusion/exclusion criteria	X															
Informed consent	X															
Anamnesis^a^	X															
Pregnancy test (serum/urine)	x*	xx*	x	x	x	x	X	x	x	x	x	x	x			
HIV, HBV, HCV test	X**															
Physical and laboratory examination^b^	X**	x***	x	x	x	x	x	x	x	x	x	x	x	x		
ECOG Performance status	X	x	x	x	x	x	x	x	x	x	x	x	x	x		
Extent of surgery^c^	x															
^11^C-MET PET/CT^d^	x															
Quality of life questionnaires^e^	x			x		x		x		x		x		x	x	
MR and RANO evaluation^f^				x (á 3 months)												
Molecular markers^g^	*To be performed during the patient's participation in the study*															
Radiotherapy **(start max. 8 weeks since surgery and max. 2 weeks after planning MR)**		x														
Chemotherapy **(start max. 8 weeks since surgery and max. 2 weeks after planning MR)**		x	x	x	x	x	x	X	x	x	x	x	x	x		
Adverse events		x	x	x	x	x	x	X	x	x	x	x	x	x	x	x
PoF analysis^h^																x

The description of performed examinations:

^*^The pregnancy test will be performed at the center (1. As part of the screening phase before 11C-methionine applications and 2. Before the 1st application of concomitant chemoradiotherapy)

^**^Laboratory analysis incl. tests for HIV, HBV and HCV will be performed in the screening phase if they have not been performed in the previous 5 days

^***^Laboratory analysis (blood count + differential + biochemistry) will be performed every week as part of CHRT. Physical examination will be performed on D1 and D21 (if not performed in the previous 5 days)

^a^Anamnesis

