## Statistical methods

### Statistical methods for primary and secondary outcomes {20a}

All data will be described for each arm separately and for the entire group of patients. The appropriate descriptive statistics will be used, i.e., counts and percentages for categorical characteristics and median and interquartile range (IQR) or mean and standard deviation (SD) for continuous characteristics. Depending on the data type, common statistical tests such as Fisher's exact test or chi-square test for comparing categorical variables and nonparametric Mann‒Whitney test or Kruskal‒Wallis test for comparing continuous variables or their parametric alternatives if the assumption of data normality is met will be used for comparison of patient characteristics between arms.

The survival parameters that will be considered are progression-free survival (PFS) and overall survival (OS). PFS is considered the time from the start of radiotherapy to the occurrence of progression or death. OS is considered the time from surgery to death (in relation to GBM). The Kaplan‒Meier method will be used to estimate the probability of survival. Survival comparisons between groups will be made using the log-rank or Gehan-Wilcoxon test. The Cox proportional hazards model will be used to calculate the hazard ratio in univariable and multivariable analyses.

All statistical tests and confidence intervals will be calculated at a significance level of 5%.

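### Overall survival is timed from surgery, but patients in both arms are selected only at the planning MR weeks later; the comparison is biased only if the arms qualify at different times (minor)

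*Protocol article*

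**What the plan says.** Outcomes {12} lists OS against Arm Ahist as a secondary outcome and defines it: "OS = time from surgery to death related to glioblastoma multiforme". Statistical methods {20a} repeats surgery as the origin. The primary endpoint has a different one: "PFS was defined as the time from the start of radiotherapy to the progression of disease or death".

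A patient becomes eligible well after surgery. Eligibility {10} requires that "Rapid early progression was detected". REP is read by comparing the early postoperative MR with the planning MR, and the latter is done "typically approx. 4–5 weeks after surgery" (Glioblastoma as a progressive disease). The abstract speaks of "Glioblastoma patients who develop REP within approximately 6 weeks after surgery". Sample size {14} describes Ahist as 44 patients with REP who were indicated for chemoradiotherapy, so the comparator was selected on the same finding.

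Tables 1 and 2 in {13} limit the start of treatment in the trial arm: "start max. 8 weeks since surgery and max. 2 weeks after planning MR". For general practice the background says: "Adjuvant therapy is usually started within 4 to 6 weeks after surgery". No surgery-to-MR or surgery-to-radiotherapy interval is given for Ahist. For survival, {20a} names Kaplan-Meier, log-rank or Gehan-Wilcoxon, and Cox; it mentions neither delayed entry nor a landmark.

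**The concern.** Anyone who died, or became unfit, between surgery and the planning MR could not be selected. The weeks before that MR are event-free by construction, yet a clock started at surgery counts them as survival. An ordinary Kaplan-Meier or Cox analysis treats every patient as at risk from day 0.

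In a randomised trial this would cancel. Here the comparator was collected in 2014–2018 and nothing balances the time from surgery to qualification. If trial patients qualify later, they carry a longer guaranteed interval and OS moves in their favour with no treatment effect; if they qualify earlier, it moves against them. At stake is whether the secondary OS comparison reflects treatment or the timing of the planning MR. Which deaths count as events is a separate matter.

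**Working it through.** The article states no OS median, hazard ratio (HR) or power, so it has no OS figure of its own to reproduce. The check asks how large a false OS difference the stated clock can create.

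**Inputs from the article.** 67 trial patients and 44 historical patients ({14}); 38 months of recruitment plus 6 of follow-up ({14}); treatment start at most 8 weeks = 56 days after surgery ({13}).

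**Assumptions.**
- Median OS is 8, 11 or 14 months.
- The hazard is constant, or rising (Weibull shape 1.5).
- Historical patients qualify at 33 days. This borrows a resection-to-radiotherapy median that the background quotes from a cited retrospective series; it is not an Ahist figure.
- Trial patients qualify later by 0, 1, 2 or 3.3 weeks.

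**Largest difference under the limit.** 56 − 33 = 23 days; 23/7 = 3.3 weeks; 23/30.4375 = 0.76 months. A 2-week difference puts trial qualification at 33 + 14 = 47 days (6.7 weeks). That is inside the limit but already later than the abstract's approximate 6 weeks. A 4-week difference gives 33 + 28 = 61 days, which breaks the limit.

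**Hand check, constant hazard, 2 weeks.** Given survival to entry at time L, median OS from surgery is L + m, where m is the median. With m = 11: historical 33/30.4375 + 11 = 12.08 months; trial 47/30.4375 + 11 = 12.54 months. The gap of 0.46 months is pure entry time. The ratio 12.08/12.54 = 0.963 is a rough guide to the false HR.

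**Simulation, no true effect.** Each patient's survival is drawn conditional on reaching qualification, OS is timed from surgery, and the test is a two-sided 5% log-rank with 2000 runs per cell. Ranges run over the three medians.

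| Trial arm qualifies later by | HR, constant hazard | HR, Weibull 1.5 | False favourable, constant hazard | False favourable, Weibull 1.5 |
|---|---|---|---|---|
| 0 weeks | 1.00–1.01 | 1.00–1.01 | 2.2–3.0% | 2.5–2.8% |
| 1 week | 0.98–0.99 | 0.99–1.01 | 2.9–4.5% | 2.6–3.4% |
| 2 weeks | 0.96–0.97 | 0.97–0.99 | 3.3–5.1% | 2.7–4.2% |
| 3.3 weeks | 0.92–0.96 | 0.96–0.98 | 4.1–6.3% | 3.9–4.4% |

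The six cells at 0 weeks average (3.0 + 2.2 + 2.3 + 2.45 + 2.8 + 2.7)/6 = 2.6%. The six at 2 weeks average (4.4 + 5.05 + 3.25 + 3.4 + 4.2 + 2.7)/6 = 3.8%. The simulation error of one cell near 4% is √(0.04 × 0.96/2000) = 0.4 percentage points. At 2 weeks with m = 11 and a constant hazard, the simulated HR is 0.964, in line with the hand check.

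**Delay after qualification.** If both arms qualify at the same time, the extra time before radiotherapy falls later, and deaths in it are counted, the HR is 0.99–1.01 and false favourable results are 2.1–3.1%. There is no bias.

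**The case against.** The strongest reply is that the event-free interval is common to both arms. Ahist was also selected on REP, REP is read on the planning MR in both, and with equal qualification times the test is unbiased. This stands, and it limits the point to a possible difference in qualification time, which the article neither reports nor rules out.

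A reader might infer more: that any longer surgery-to-radiotherapy interval in the PET arm is credited as an OS gain. The documents do not support this, for three reasons.

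- The guaranteed interval ends at qualification, not at radiotherapy. PET follows the detection of REP, so a death in a PET-related delay counts for an enrolled patient. Such a delay creates a false gain only if later radiotherapy is assumed to postpone death by the same amount. Under that assumption false favourable results reach 5–8% at 3.3 weeks, but nothing in the article justifies it.
- Setting the 8-week limit against the usual 4 to 6 weeks compares a maximum with a typical range. It does not show that the PET arm starts later, and the background stresses starting treatment quickly in REP.
- Different origins for PFS and OS are not a contradiction. Surgery is a declared origin and is the same in {12} and {20a}.

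One counterpoint survives in part. Tables 1 and 2 place consent and PET within a screening period of up to 14 days, and {20c} builds the Full Analysis Set from patients who completed recruitment. A patient who dies during screening may therefore never be analysed, and the event-free interval could run somewhat past the MR. The article does not settle this.

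Delayed entry could also be set out in an analysis plan that is not shown. That lowers the weight of the point, but the definition and the methods in {20a} as written do not fit the selection.

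**Conclusion.** The point holds in a limited form. The OS clock starts weeks before a patient in either arm could be selected, and the stated analyses do not handle that interval. The comparison is unbiased if both arms qualify at the same time after surgery, and no difference is documented. With a 2-week later qualification in the trial arm, the false HR is about 0.96–0.99 and false favourable results are about 4% instead of 2.5%. At the 3.3 weeks that the 8-week limit allows, they are about 4–6%. Earlier qualification would bias the other way. These sizes rest on the assumed medians, hazard shapes and 33-day historical interval. The endpoint is secondary; severity is minor.

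**What to change.** In {12} and {20a}, align OS with eligibility in both arms. Either keep surgery as the origin and let each patient enter the risk set at the qualifying planning MR (delayed entry in Kaplan-Meier, log-rank and Cox), or time OS from that MR. In the scenarios simulated, delayed entry at the MR was neutral or better than the stated analysis. It assumes that time to qualification is not itself prognostic.

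Report OS from the start of radiotherapy as a sensitivity analysis only. With a 3-week delay after qualification, a median of 11 months and Weibull shape 1.5, timing from radiotherapy gave 1.5% false favourable and 4.0% false unfavourable results, a slight bias against PET. It also leaves patients who die before radiotherapy without valid follow-up. It is still useful as a check on any event-free time during screening.

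Tabulate the surgery-to-MR and surgery-to-radiotherapy intervals by arm, so that readers can see whether the arms differ.

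The cost is a few sentences and a little extra analysis. The MR date is needed to establish REP in both arms, and the surgery and radiotherapy dates are needed for OS and PFS. OS timed from the MR will read about 1 month shorter than OS from surgery (4–5 weeks / 4.345 = 0.9–1.2 months).

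### The pattern-of-failure comparison treats several progressions in one patient as independent units, so its 5% level is not assured, and the in-field category has no upper bound

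*Protocol article*

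**What the plan says.** All the relevant text on the outcome is in the protocol article, Outcomes {12}, under the pattern-of-failure analysis.

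- **Comparison.** Patterns of failure are evaluated "in patients with REP (the Experimental Arm) compared to the historical retrospective group (Arm Ahist"), so this is a between-arm contrast and not only a description.
- **Reading of images.** "In the case of multifocal progression, each PD is evaluated independently, i.e., the patient could have one central and one distal PD".
- **Statistical unit.** A separate sentence carries this into the analysis: "In subsequent statistical analysis, each PD was evaluated independently".
- **Categories.** "central (V95% ≥ 95%)/in-field (80% ≤ V95%)/marginal (20% ≤ V95% < 80%)/distant (V95% < 20" per cent).

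Statistical methods {20a} names "common statistical tests such as Fisher's exact test or chi-square test for comparing categorical variables". In that sentence the tests serve to compare patient characteristics between arms. No test is named for pattern of failure, and neither clustering nor a patient-level summary is mentioned. The same section adds: "All statistical tests and confidence intervals will be calculated at a significance level of 5" per cent.

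**The concern.** Grading each focus separately is sensible image reading. Treating each focus as a separate independent observation in the analysis is a different step, and the article takes it explicitly. Two foci in one patient arise from the same tumour and were irradiated under the same plan, so their categories cannot be presumed independent. Any test or interval that counts them as independent uses the wrong amount of information.

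The number of foci is also an outcome and may differ between arms. A PD-level share therefore mixes how many foci patients develop with where they develop.

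This matters because Objectives {7} rests on PET revealing aggressive areas that MR misses, so that radiotherapy can be planned better. Pattern of failure is the outcome that looks most directly at that mechanism.

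The category list raises a smaller, separate problem: a PD with V95% of 95% or more satisfies both the central and the in-field definitions.

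**Working it through.** **Stated figures.** The article gives no sample size, power, foci count, correlation or category share for pattern of failure, so there is no figure of its own to reproduce.

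**Inputs from the article (Sample size {14}).** There are 44 historical patients and 65 events needed. The check takes 65 versus 44 progressing patients; treating 65 as the Experimental Arm count, and assuming every one of these patients has a classifiable progression, are assumptions.

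**Other assumed inputs.** Share of multifocal patients, foci per multifocal patient (m), intraclass correlation (ICC), and a 25% share for the category compared, with no true difference between arms.

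**Step 1, design effect.** DE = 1 + (E[m²]/E[m] − 1) × ICC, and true alpha ≈ 2 × (1 − Φ(1.96/√DE)).

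Example with 40% bifocal and ICC 0.5:
- E[m] = 0.6 × 1 + 0.4 × 2 = 1.4 and E[m²] = 0.6 × 1 + 0.4 × 4 = 2.2.
- DE = 1 + (2.2/1.4 − 1) × 0.5 = 1.286.
- 1.96/√1.286 = 1.73, so alpha ≈ 8.4%.
- The 109 patients yield 109 × 1.4 ≈ 153 PDs, worth about 153/1.286 ≈ 119 independent ones.

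**Step 2, simulation.** PD-level tests at 5%, 8,000 runs per scenario. The Monte Carlo standard error near 5% is √(0.05 × 0.95/8000) ≈ 0.24 percentage points.

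| Assumed scenario | DE | Alpha from DE | Chi-square, simulated | Fisher, simulated |
|---|---|---|---|---|
| One PD per patient | 1.00 | 5.0% | 4.7% | 3.7% |
| 20% with 2 foci, ICC 0 | 1.00 | 5.0% | 4.9% | 3.8% |
| 20% with 2 foci, ICC 0.5 | 1.17 | 7.0% | 6.8% | 5.5% |
| 40% with 2 foci, ICC 0.5 | 1.29 | 8.4% | 8.6% | 7.1% |
| 50% with 3 foci, ICC 0.5 | 1.75 | 13.8% | 12.5% | 11.0% |
| 20% with 2 foci, ICC 1 | 1.33 | 9.0% | 9.4% | 7.6% |
| 40% with 2 foci, ICC 1 | 1.57 | 11.8% | 12.3% | 10.5% |
| 50% with 3 foci, ICC 1 | 2.50 | 21.5% | 21.5% | 19.7% |

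**Step 3, discordant foci.** With a 25% share, the lowest possible correlation between two foci is −0.25/0.75 = −0.33. The design-effect formula then gives about 3.8% with 20% bifocal patients and 3.0% with 40%, so the test becomes conservative.

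**Step 4, weighting.** Suppose 10% of first foci are distant in both arms, every second focus is distant, and bifocal progression occurs in 40% versus 20% of patients. The PD-level distant share is (0.10 + 0.40)/1.40 = 36% versus (0.10 + 0.20)/1.20 = 25%, although first-focus patterns are identical.

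**Step 5, categories.** Take illustrative true shares of 60% central, 15% in-field, 10% marginal and 15% distant. Applied literally, in-field becomes 60% + 15% = 75%, and the four sum to 60 + 75 + 10 + 15 = 160%. Read in order, with central taken first, they sum to 100%. The marginal and distant bounds overlap with nothing.

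**The case against.** The strongest reply is that the harm is not demonstrated, and several parts of it stand.

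- A reader might infer that the p-values are wrong, or that the error rate is inflated. The article does not support this. Multifocality and correlation are not given, and its only example, one central and one distal PD in a patient, is a discordant pair. With few bifocal patients and Fisher's test, the error can stay close to 5%.
- A reader might infer that Fisher's or the chi-square test is assigned to this outcome. It is not: {20a} names them for patient characteristics, and the exact test may be left to a fuller document. The independence rule, however, is stated in the article, and any test that follows it has the same weakness.
- A reader might call the PD-level proportions wrong. They are a legitimate description of progressions. They answer a different question from patient-level proportions.
- A reader might infer that multifocal patients dominate the distant category. Nothing in the article shows this; the weighting example shows only that it could matter.
- The category overlap is a wording matter. Reading the list in order resolves it, although no order is stated, and a contrast on marginal or distant failure is untouched.
- Pattern of failure is one of many secondary outcomes, compared with a nonrandomised historical arm. Clustering is only part of its uncertainty.

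Not knowing the direction of the error is no defence of the rule. It means that the 5% level claimed in {20a} is not assured either way.

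**Conclusion.** The point holds in limited form. The article fixes the PD as an independent statistical unit while allowing several per patient, so nominal p-values and confidence intervals for this comparison are not reliable, and patients with more foci weigh more. At an assumed ICC of 0.5, type I error ranges from about 5.5% (Fisher, 20% bifocal) to 12.5% (chi-square, half with three foci). It returns to the nominal level or slightly below at zero correlation, and falls further with discordant foci. All of these figures rest on assumed multifocality, correlation and category share, and on 65 versus 44 classifiable patients; none is a prediction for this trial.

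The missing upper bound on in-field is a separate and smaller defect, confined to the central/in-field split. Both should be corrected. Neither touches the primary PFS analysis.

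**What to change.** 1. Keep the separate reading of each focus, but replace the sentence on independent evaluation in the statistical analysis. State that PDs are compared between arms with inference clustered by patient: GEE with robust standard errors, a cluster bootstrap, or a cluster-adjusted chi-square.
2. Add a patient-level summary, for example any marginal or distant component (yes/no), compared with Fisher's exact test. Report it beside the PD-level result, not in place of it: it drops the central/in-field distinction, and patients with more foci have more chances of a yes.
3. Write in-field as 80% ≤ V95% < 95%, which makes the four categories exclusive and exhaustive.

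The cost is a few lines of wording and code and, where foci are positively correlated, slightly wider intervals. No new data are needed and patient care does not change.
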